### Randomization, allocation, and concealment

Eligible participants at each elderly center will be randomly assigned to either an EG or a WLCG using a computer-generated allocation sequence with a 1:1 ratio, facilitated by Research Randomizer (Research Randomizer Version 4.0; www.randomizer.org). Participants living in the same household will be randomized as a single unit to reduce the influence of their dietary habits on each other. The allocation sequence will be documented and placed in sealed envelopes, which will be opened after participants complete a baseline questionnaire. They will then be informed of their group assignment and follow-up procedures. The healthcare team and research assistants will remain blind to group allocations. All participants in the EG will receive the intervention as per the established protocol, with follow-up sessions scheduled on different dates for each group to prevent contamination and maintain blinding for assessors.

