### Intervention protocol

The intervention protocol is reported based on Template for Intervention Description and Replication (TIDieR) checklist and guide [79]. Prior to the commencement of the 12-week intervention, a two-day workshop will be conducted to introduce five key domains: (1) health risk appraisal and self-care; (2) PA and self-administrated acupressure; (3) emotion and stress management; (4) WFPB diet, nutrition, and disease relationships; and (5) meditation and mindfulness practices. This workshop is led by a multidisciplinary team comprising the principal investigator, registered TCM practitioner, senior physiotherapist (SPT), fitness trainer, registered dietitian, mindfulness instructor, senior registered nurse, and WFPB medical doctor. CMs are required to attend the workshop to familiarize themselves with the intervention content and the operations of the eHealth system. On the final half-day of the workshop, the eHealth system will be distributed to all EG participants. A briefing and hands-on training session will be organized by the information technology provider and technicians to demonstrate the operation of the eHealth system. All EG participants will be guided to learn self-monitoring logbooks to record their WFPB diet, physical exercise, mindfulness practices and a stress management logbook during the joint training and demonstration. An e2HLE booklet will be provided to all EG participants, encompassing a range of topics (Table 2).

**Table 2 Tab2:** The details of the e2HLE booklet

**Component**	**Details**
PA and self-administrated acupressure	-The importance and key points of PA; warm-up exercise, stretching, balance training, muscle strength training, aerobic exercise, cool down exercise with photos, URL links and QR codes. -The origin, efficacy and operating techniques of acupressure and self-administrated acupressure methods for the twelve most common acupressure points (e.g., GV20 Baihui, GB20 Fengchi, GB21 Jianjing, BL52 Zhishi, LI10 Shousanli, ST36 Zusanli, LI4 Hegu, SP6 Sanyinjiao, BL40 Weizhong, KI1 Yongquan, etc.)

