### Procedure of data collection

Eligible participants will be invited to join the study after providing signed consent following a detailed explanation of the study’s purpose and procedures. Baseline data (T1) will be collected by trained assessors. After the 12-week intervention, assessors who are blinded to group allocations will conduct physical assessments. Participants will complete questionnaire surveys, including health examinations, using a secure institutional account in Qualtrics to ensure data privacy. They will fill out the baseline questionnaire and health examination before randomization and participate in a follow-up interview approximately three months later (T2). A structured questionnaire will collect data, with only demographic information gathered at T1, and all measurements will be administered in Cantonese, consistent with previous Hong Kong studies. Appendix C details the outcome measures, assessment methods, and psychometric information.

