### Pre- and post- blood tests

A total of 20 ml of blood will be drawn and tested by medical professionals in a designated laboratory. The blood tests will cover five main categories: (1) Albumin (nutritional marker); (2) CRP (inflammation marker); (3) Total blood cell count, creatinine, BUN, liver function tests, blood sugar levels, and HbA1c (indicators of anemia, diabetes, and organ function); (4) Total cholesterol, HDL, and LDL levels (cardiovascular disease risk factors); and (5) Homocysteine (indicating potential vitamin B-12 or folate deficiency). Individualized sessions lasting 15 to 20 min will be held for all EG participants after receiving their pretest and posttest blood reports, approximately 2 to 3 weeks after the intervention starts and ends. During these sessions, a registered dietitian and/or a WFPB medical doctor will provide explanations and advice for follow-up care. If any blood test results are abnormal, appropriate referrals for further treatment will be recommended.

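### The blinding claim cannot hold for the clinicians who deliver the intervention, and holding follow-up on separate dates by arm works against assessor blinding

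*Protocol article*

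**What the plan says.** All references are to the protocol article.

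- **Randomization, allocation, and concealment**, on staff: "The healthcare team and research assistants will remain blind to group allocations". On scheduling, the same paragraph ends with "follow-up sessions scheduled on different dates for each group to prevent contamination and maintain blinding for assessors".
- **Procedure of data collection**: after the intervention, "assessors who are blinded to group allocations will conduct physical assessments". Participants complete baseline before randomisation and then "participate in a follow-up interview approximately three months later (T2").
- **Intervention protocol**, on the workshop that opens the EG programme: "This workshop is led by a multidisciplinary team comprising the principal investigator, registered TCM practitioner, senior physiotherapist (SPT), fitness trainer, registered dietitian", followed by a mindfulness instructor, a nurse and a doctor. Until crossover at 12 weeks, WLCG receives only the centres' usual care.
- **Pre- and post- blood tests**: "Individualized sessions lasting 15 to 20 min will be held for all EG participants after receiving their pretest and posttest blood reports", and in them "a registered dietitian and/or a WFPB medical doctor will provide explanations and advice for follow-up care". No such sessions are described for WLCG before crossover.
- **Planned data analysis**: research assistants help to cross-check the process-evaluation transcripts. Under Intervention protocol, the participant process-evaluation sessions belong to the intervention, so before crossover they are EG sessions.

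**The concern.** There are two linked problems.

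First, the article claims blinding for staff who, on its own description, know who is in EG. If the sentence passes into the trial report, it will claim a safeguard that did not exist for those staff.

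Second, the scheduling rule is offered as protection for assessor blinding but tends to do the opposite. Assessors can stay blind in a trial with unblinded participants only if one participant's allocation says nothing about the next participant's. Single-arm dates remove that independence. They also mean that whatever is peculiar to a date (the assessor on duty, the room, equipment set-up, a nearby holiday) falls on one arm only.

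At stake is the credibility of outcomes where the assessor's handling matters: waist circumference, blood pressure and motor function.

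**Working it through.** The plan gives no figure on this point, so the check is mainly a comparison of its statements.

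**Step 1. Can the healthcare team be blind?**

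| Staff described | Contact before T2 | Can be blind to EG membership? |
|---|---|---|
| Workshop leaders, including physiotherapist, dietitian, nurse and doctor | Lead the workshop for EG | No |
| Dietitian and/or doctor | Individual pretest blood-report sessions with EG, about 2 to 3 weeks after the intervention starts | No |
| Research assistants | Cross-check process-evaluation transcripts | Only if this work is kept apart from T2 data collection |
| T2 assessors | Physical assessments | Yes, if they have no role above and the schedule does not reveal arm |

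Healthcare team is not defined. The article describes no separate clinical team that cares for both arms without intervention contact. For the first two rows the blinding statement is contradicted.

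**Step 2. What are the follow-up sessions?** Two readings are possible.

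- *T2 assessment visits.* The rule applies to each group, its stated purpose includes assessor blinding, and T2 is itself called a follow-up interview. WLCG has no intervention sessions before T2, so there would otherwise be nothing of theirs to schedule in that period.
- *Intervention contacts.* The sentence begins with EG receiving the intervention, and preventing contamination is a usual reason for separating such contacts. On this reading the rule says nothing about how assessors meet participants at T2, so it cannot be what keeps them blind.

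The first reading fits better. On the second, the stated rationale still fails.

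**Step 3. What follows if T2 dates are single-arm?** Suppose *m* people are seen on a date and one of them mentions the tablet, the diet or the workshop.

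- Single-arm date, with an assessor aware that dates are not mixed: allocations revealed = *m*, the whole session.
- Mixed date: allocations revealed = that person, plus any household member randomised in the same unit.

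This follows from the design. It does not estimate how often disclosure happens.

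**Step 4. Aliasing of date with arm.** With one date per arm at a centre, the observed difference there is treatment effect + (date effect on EG's date − date effect on WLCG's date), and the two parts cannot be separated. Several interleaved dates per arm would let date effects partly average out, but the article does not say whether dates are interleaved or how far apart they are.

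**Step 5. Size.** No date effect can be taken from the documents. Purely to show the scale, *assume* a systematic between-arm shift of δ standard deviations, with 70 per arm (Sample size section) and a two-sided 5% test. The standard error is √(2/70) = 0.169, and

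P(reject when there is no treatment effect) = 1 − Φ(1.96 − δ/0.169) + Φ(−1.96 − δ/0.169).

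| Assumed δ | Type I error |
|---|---|
| 0 | 5% |
| 0.05 | about 6% |
| 0.10 | about 9% |
| 0.20 | about 22% |

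The true δ may be zero. The table describes sensitivity to an assumption and is not a finding about this trial.

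**The case against.** The strongest defence has four parts.

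1. *Separate dates do not by themselves unmask anyone.* An assessor must learn which arm a date belongs to, and mixed dates also allow disclosure, one person at a time. This stands. A reader might infer that assessors will certainly be unmasked, but the documents do not support that. The supported statement is that the rule turns an individual disclosure into a session-wide one.

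2. *No gap between the arms' dates is stated.* This stands too. A reader might infer that season or length of follow-up differs systematically by arm, because EG's 12 weeks begin after a workshop. The documents do not show it: different dates could be adjacent days, one timing of about three months applies to everyone, and a two-day workshop plus 12 weeks fits that timing.

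3. *Few outcomes are exposed.* Largely right. Weight is read from the same electronic scale, blood markers come from a laboratory, heart rate variability and recovery come from the device, and participants largely complete the questionnaires themselves. Aliasing with date could in principle reach weight, but assessor influence on it should be small.

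4. *The healthcare team may be some other group,* such as those who draw blood. The term is undefined, so it goes too far to say that no healthcare worker could be blind. For the clinicians under Intervention protocol and Pre- and post- blood tests, however, the statement cannot be true, and the text does not exclude them.

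Contamination is also a stated aim of separate dates, and participants who meet at T2 could talk before completing self-reports. That is a real but limited cost, since the randomised comparison is ending.

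**Conclusion.** The point holds in two parts.

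- **Blinding claim.** It contradicts the described roles of the workshop leaders and of the dietitian and/or doctor who counsels EG on blood reports. This needs no assumption about bias, only that healthcare team includes the sole clinical team the article describes.
- **Scheduling rule.** On the better reading, that follow-up sessions are T2 assessments, single-arm dates make date a marker of arm and alias measurement date with treatment. This weakens the blinding the rule is meant to protect.

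The size of any bias cannot be derived from the documents. The risk falls mainly on waist circumference, blood pressure and motor tests. Nothing here shows that the weight comparison is biased. The correction is worth making because it is cheap and because the blinding statement would otherwise be reported as it stands.

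**What to change.** 1. Replace the statement on the healthcare team and research assistants with one limited to T2 outcome assessors, and to research assistants collecting T2 data, who have no part in delivery or process evaluation. State that delivery staff are not blind.
2. Say what follow-up sessions means. Keep separate dates for intervention sessions only, with contamination as the reason.
3. Hold T2 for both arms on the same dates at each centre, in mixed order, within a common window counted from randomisation and before any WLCG intervention contact. Appointments can be booked from the randomisation date without reference to arm.

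The cost is a few sentences and a different appointment plan, with no extra participants or measurements. The drawback is that people from the two arms may meet at T2.

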### Intervention materials and theoretical framework

The eHealth system is designed to facilitate the implementation of a personalized, goal-based health care plan, enabling participants to monitor their health vitals at home on a weekly basis and engage in weekly tele-counseling sessions. The system comprises the following components: (1) temperature and oxygen monitoring (single-sided bio-sensing earbud for the right ear); (2) tablet; (3) FDA-certified Bluetooth blood pressure monitor; (4) docking station; (5) USB charging cable; (6) anti-static bag; (7) three ear gels (medium size); and (8) user manual. Additionally, a 5G data plan will be provided to all EG participants. The eHealth system captures seven key health vitals: heart rate, respiratory rate, core body temperature, oxygen saturation (SpO2), HRV as an indicator of mental health, HRR for cardiac health, and blood pressure.

The front page of the eHealth system (Fig. 3) features a visually engaging user interface and user experience design that directs participants to six icons for self-monitoring logbooks and an educational section: (1) daily recording of WFPB dietary details; (2) documenting daily PA, accompanied by relevant video materials; (3) recording mindfulness practices; (4) monitoring and capturing seven health vitals; (5) documentation of a stress diary, thought records, and pleasant events; and (6) comprehensive information on MetS, psychosomatic symptoms and their health risk factors, as well as self-care strategies. Additionally, the eHealth system incorporates a calendar reminder feature for tele-counseling sessions and employs “cues to action,” highlighted in red with an exclamation mark, to promote self-initiated action and self-regulation among participants.

**Fig. 3 Fig3:**
[figure not shown]
The launcher of the home-based self-monitoring bio-signals eHealth system for the e2HLE intervention

Four recognized heuristic frameworks commonly guide complex interventions: the RE-AIM framework, the Conceptual Model of Implementation Research, the Consolidated Framework for Implementation Research, and the PICO framework. Additionally, Parkinson et al. [78] proposed a multi-component evaluation framework that examines micro, meso, and macro levels to identify mechanisms for enhancing engagement and success in interventions. Our study utilizes a similar framework to assess the effectiveness, acceptability, fidelity, generalizability, sustainability, uptake, implementation costs, and scalability of a holistic lifestyle intervention in real-world social contexts (see Fig. 1).

### Adherence and fidelity

Throughout the 12-week intervention, self-monitoring logbooks within the eHealth system will be utilized to record WFPB diets, PA, and mindfulness practices (Appendix B). Dietary adherence will be quantified using a dietary adherence score derived from the food records. Initially, the food records will be analyzed using Food Processor software, version 11.1, developed by ESHA Research (Salem, Oregon, USA), to determine the nutrient and energy intake associated with each diet plan. Apart from the nutrient and energy intake, it is crucial to assess whether EG participants are consuming a diverse and abundant array of high quality whole plant-based foods, including leafy greens, cruciferous vegetables, rhizomes, solanaceous vegetables, legumes, beans, soy products, whole grains, nuts, and seeds.

Additionally, all EG participants are instructed to wear a single-sided earbud via the eHealth system while watching and following the exercise videos to facilitate simultaneous monitoring and capturing of their health vitals. Regarding mindfulness practices, participants will be required to log whether they engage in meditation, including the duration and types of meditation techniques practiced. Adherence to self-monitoring will be tracked over the course of the 12-week intervention. This adherence will be quantified by calculating the percentage of completed logbooks relative to the total number of logbooks targeted.

Starting in the third week of the intervention, EG participants are required to complete a stress management logbook within the eHealth system (Appendix B). Case managers (CMs), who are registered social workers, will facilitate discussions with EG participants to reinforce and remind them to apply the coping strategies they have learned.

The speech-to-text (STT) software is integrated into the tablet and facilitated by the eHealth system, allowing EG participants to input the aforementioned details either by audio or using a stylus pen for text entry. Audio recordings will be converted to text and transferred to the backend system, where CMs can retrieve and download these text files. CMs are required to review the logbooks and bio-signal files to implement and assess a goal-based health care plan in collaboration with EG participants prior to the weekly tele-counseling sessions. If participants experience any discomfort or difficulties during the intervention period, they will be referred to appropriate specialists.

Attendance for the 2-day workshop and the 12 weekly theme-based sessions will be monitored to ensure adherence to the intervention activities. Attendance will be calculated as a percentage of sessions attended relative to the total number of targeted sessions. Both attendance and self-monitoring will serve as common indicators of adherence. Previous research has indicated that when attendance distribution skews toward the higher end, attendance can be categorized into high (≥ 80%) or low (< 80%) adherence groups for analytical purposes [70].

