### Sample size

Based on the literature review on previous similar RCTs [63], Cohen’s d ranges from 0.2 to 0.5 for small effect and from 0.5 to 0.8 and greater than 0.8, for medium and larger effects respectively. To detect a medium effect size of 0.5, 140 participants (126/1-0.1.1.1 = 140) are required (70 participants in each arm) to achieve a statistical power of 80% at the 5% significance level (alpha = 0.05, 2 tails). Based on the attrition rate of 8% in the pilot study at 3 months that was conducted in 2021/22, it is estimated to recruit 75 participants per group (i.e. 150 in total).

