### Planned data analysis

Data will be entered and analyzed using SPSS version 30. Demographic data will be summarized, with frequency and percentage for categorical variables, and mean and SD for continuous variables. Group difference at baseline will be compared using chi-squared tests for categorical variables and ANOVA for continuous variables. The Pearson correlation will be used to explore the relationship between weight loss and adherence scores. Changes in variables between baseline and the three-month follow-up will be compared using paired t-tests or Wilcoxon signed-rank tests as appropriate. To compare the mean changes in the continuous outcome variables including body weight, waist circumference, BMI, HRV and HRR, sleep quality, nutritional status, self-care capacity, perceived depressive symptoms and stress level, chronic pain among the two groups with the intention-to-treat principle. This approach ensures that all participants are included in the analysis as originally assigned, regardless of their level of compliance, thereby mitigating the impact of missing data. For missing values, methods like multiple imputation and sensitivity analyses will test the robustness of results. Adherence rates will also be analyzed alongside outcomes, using generalized estimating equations to account for repeated measures and reliably estimate intervention effects. Medication use for metabolic diseases and psychosomatic symptoms will be documented at baseline and follow-up, serving as a covariate in analyses to distinguish intervention effects. Subgroup analyses may compare outcomes between medicated and non-medicated participants. As age may significantly influence participants’ responsiveness to the intervention, conducting subgroup analyses by age cohort offers more specific insights into how the intervention may benefit older adults at different stages of aging. Post hoc pairwise comparisons of the changes in the outcome variables across the two study groups will be performed to compare the effectiveness of the EG and the WLCG. All the tests are two-sided and a *p* < 0.05 will be considered statistically significant.

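### The plan lets attendance, recorded as a percentage, be split at 80% for analysis if it proves skewed upwards; skew does not justify the split, and the exploratory adherence analysis would lose dose information

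*Protocol article*

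**What the plan says.** The Adherence and fidelity section of the protocol article sets what is counted ("Attendance for the 2-day workshop and the 12 weekly theme-based sessions will be monitored") and the scale: "Attendance will be calculated as a percentage of sessions attended relative to the total number of targeted sessions". Attendance and self-monitoring are both named as indicators of adherence.

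The same paragraph then turns to the form used in analysis. It opens with "Previous research has indicated that when attendance distribution skews toward the higher end" and concludes that "attendance can be categorized into high (≥ 80%) or low (< 80%) adherence groups for analytical purposes". The wording is permissive and rests on a cited study. It is also the only statement in that section on how attendance would be handled in analysis.

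The Planned data analysis section contains no 80% split. It says "The Pearson correlation will be used to explore the relationship between weight loss and adherence scores" and, further on, "Adherence rates will also be analyzed alongside outcomes, using generalized estimating equations". It does not say whether attendance enters as the percentage or as two groups.

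**The concern.** Three features of the optional split are weak.

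- **The trigger is not a valid reason.** Neither linear regression nor generalized estimating equations assume a normally distributed explanatory variable. If upward skew raises a worry about standard errors or influential low attenders, other tools deal with it and keep the scale.
- **The choice of scale follows the data.** The 80% threshold is fixed in advance, but whether it is used depends on the observed distribution. The analysis section describes numeric analyses, so two scales are open for one question.
- **Dose information is lost.** Everyone below the threshold is treated alike, and near neighbours on either side of it are separated.

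At stake is the planned look at whether greater participation goes with greater weight loss. Only people who receive the programme have attendance to analyse, so in the randomised period this rests on one arm of about 75.

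**Working it through.** **1. The plan's own figure.** No power is stated for any adherence analysis. The Sample size section covers only the two-arm comparison ("To detect a medium effect size of 0.5, 140 participants", "statistical power of 80% at the 5% significance level (alpha = 0.05, 2 tails").

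- Per arm: 2 × (1.960 + 0.842)² / 0.5² = 62.8, so 63, and 126 in total.
- With 10% inflation: 126 / 0.9 = 140, as stated.
- With the 8% pilot attrition: 140 / 0.92 = 152.2, against 150 stated, which is close.

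The attendance split enters none of this.

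**2. Number available for the adherence analysis.** 75 in the experimental group, or 75 × 0.92 = 69 after 8% attrition.

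**3. What the cut does on the actual scale.** Two workshop days plus 12 sessions make 14 units if each day counts once.

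- 14 units: 0.80 × 14 = 11.2, so 12 of 14 (85.7%) is high and 11 of 14 (78.6%) is low. The low group runs from 0 to 11 units.
- 12 sessions only: 0.80 × 12 = 9.6, so 10 of 12 (83.3%) is high and 9 of 12 (75.0%) is low.

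Someone who attended 3 of 14 (21%) is grouped with someone who attended 11 of 14 (79%).

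**4. Analytic check (assumes normally distributed attendance and a linear relation).** Power ≈ Φ(atanh(r) × √(n − 3) − 1.960). Cutting at a point that leaves a share p on one side multiplies r by φ(z_p) / √(p(1 − p)), which is 0.798 for a 50:50 split and 0.700 for 80:20. For r = 0.30, n = 69 and a 50:50 split:

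- Percentage: 0.3095 × 8.124 − 1.960 = 0.554, so power is 0.710.
- Split: r becomes 0.239; 0.244 × 8.124 − 1.960 = 0.023, so power is 0.509.
- Loss: 20 points.

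Over r = 0.2 to 0.4 and n = 69 to 75, the loss is 12 to 20 points for 50:50 and 17 to 32 points for 80:20.

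**5. Simulation with upward-skewed attendance (two-sided 5%, linear relation).** Attendance was beta-binomial. For n = 75, it ran over 12 or 14 units with 46 to 77% of participants at or above 80%. For n = 69, it ran over 14 units with mean 80 to 90%, and the low group held 21 to 45% (about 14 to 31 people).

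| n | r | Power, percentage | Power, 80% split | Loss (points) |
|---|---|---|---|---|
| 75 | 0.2 | about 0.41 | 0.27–0.31 | 10–14 |
| 75 | 0.3 | about 0.75 | 0.53–0.59 | 15–22 |
| 75 | 0.4 | about 0.95 | 0.81–0.85 | 10–14 |
| 69 | 0.30 | 0.70–0.72 | 0.53–0.56 | 14–19 |
| 69 | 0.35 | 0.83–0.84 | 0.67–0.69 | 14–17 |
| 69 | 0.40 | 0.92–0.93 | 0.80–0.81 | 11–13 |

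With milder skew (34 to 41% at or above the cut, n = 75), the loss is 14 to 25 points.

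**6. When the sign reverses.** If the true effect is a step exactly at 80% (n = 75, 12 sessions), the split does better: 0.55 against 0.41 for a step of 0.5 SD, and 0.82 against 0.65 for a step of 0.7 SD.

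**The case against.** The sentence reports what earlier research did and says what can be done, not what will be done. The trial's own commitment is to compute a percentage, and the analysis section plans numeric analyses without mentioning a split. The only adherence measure that the article calls a score is the dietary one, so the Pearson correlation may not concern attendance at all. The power loss depends on assumed inputs and can turn into a gain. The analysis is exploratory and has no power target, and coding details of this kind are often left to a full analysis plan.

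Much of this stands. A reader might infer that the trial has committed itself to cutting attendance at 80%, or that a definite number of power points will be lost. The text supports neither: the wording is permissive, nothing says the split would replace the percentage, and no correlation, attendance distribution or dose-response shape is given. Nor do the documents suggest any effect on the body-weight comparison between arms.

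What survives is narrower. The article does not leave the coding unsaid. It puts forward one specific option for analysis, gives skew as its condition, and does not reconcile it with the numeric analyses described later. If the Pearson analysis is confined to the dietary score, attendance can still enter through the analysis of adherence rates. The documents give no reason to expect a step at exactly 80%.

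**Conclusion.** The point holds as a minor one. The plan permits a split of a recorded percentage on a ground, skew, that does not justify it, and it leaves the scale open until the data are seen.

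Under assumptions that the documents do not supply (69 to 75 experimental-group participants, upward-skewed attendance, a linear relation, r = 0.2 to 0.4), the split would cost roughly 10 to 20 points of power if used in place of the percentage. Individual settings go somewhat above that, and a true step at 80% would make it a gain. The consequence is confined to an exploratory association.

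**What to change.** In the Adherence and fidelity section, replace the sentence on categorising skewed attendance with a statement of this content: attendance and self-monitoring enter the adherence analyses of the Planned data analysis section as percentages, for example as weight change per 10 percentage points attended, with robust standard errors specified in advance whatever the skew. Keep the 80% split as a descriptive count of participants, without a test.

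A switch to rank correlation only if attendance is skewed is not a good substitute. It is again a choice triggered by the data, and under heavy skew it recovered as little as about 1 point of the lost power.

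The change needs no new data. The one small downside is that a slope is slightly less simple to present than a high-versus-low contrast.
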